## **9.3 Study Procedures**

### **9.3.1 Study Materials**

Study documents (e.g. Case Report Forms (CRFs), drug accountability logs, etc.) will be provided by the sponsor, the study site and/or a contracted designee. Specimen collection supplies (e.g. collection tubes and requisitions) for clinical assessments will be provided by the site or clinical safety laboratory.

### **9.3.2 Subject Background Assessments**

#### **9.3.2.1 Demographics & Medical/ Psychiatric History**

A complete medical and psychiatric history will be obtained from subjects at the times indicated in Sections 9.1 and 9.2. Demographic information, including date of birth, gender, race and ethnicity will be recorded as well. Any new medical conditions reported prior to initial informed consent will be reported on the Medical History section of the subject study records while new updates after initial informed consent will be captured as AE.

#### **9.3.2.2 Structured Clinical Interview for DSM-5 Disorders – Clinical Trials Version (SCID-5-CT)**

The SCID-5-CT will be administered and reviewed by a qualified clinician or rater at the Initial Screening Visit to confirm a subject's study eligibility. Results are to be included in the subject's

study record.

### 9.3.2.3 Height

Height will be measured at the Initial Screening Visit only. The height measurement should be recorded in centimeters (cm) in the subject's study records.

### 9.3.2.4 Body Weight

Body weight will be measured at specified timepoints indicated in Sections 9.1 and 9.2. Results of the body weight are to be recorded in kilograms (kg) in the subject's study records.

### 9.3.2.5 Body Mass Index (BMI)

BMI will be calculated and recorded at the Initial Screening Visit only using the following formula:  $\text{Weight (kg)} / [\text{height (m)}]^2$

## 9.3.3 Safety Assessments

### 9.3.3.1 Physical Examination (including a neurological examination)

A physical examination (including a neurological examination) will be performed at specified timepoints indicated in Sections 9.1 and 9.2. The physical examination will include, but not be limited to, assessments of the following:

- General Appearance
- Head/ Face
- Eyes
- Ears/Hearing
- Nose
- Mouth, Teeth and Throat
- Neck & Thyroid
- Chest/Lungs
- Abdomen
- Skin, Hair, and Nails
- Musculoskeletal: Extremities, Spine
- Vascular/Circulatory
- Lymphatic
- Psychiatric/Behavior
- Neurologic (see below)

### **The neurological examination will include assessments of the following:**

- Cranial Nerves Function: Reactivity to Light, Accommodation of pupils, and Extraocular Eye Movements
- Coordination: Finger to Nose, Finger Tapping, Rapid alternating Hand Movements, Gait, and Romberg Test
- Deep Tendon Reflexes: Brachioradialis, Patellar, and Achilles
- Presence of Tremors: Resting, Postural, and Intension

- Sensory Exam: Pin Prick and Tactile Soft Touch
- Motor System: Spastic gait, Cerebellar ataxia, Sensory ataxia, Akinetic-rigid gait, Step age gait, Upper/Lower body strength
- Mental Status

The results of the physical examination are to be recorded in the subject's study records. Any clinically significant changes from baseline should be recorded as an AE.

### 9.3.3.2 Vital Signs

Vitals signs will be collected at specified timepoints indicated in Sections 9.1 and 9.2.

Vital signs will include oral body temperature (°C), supine respiration rate, systolic and diastolic blood pressure (SBP, DBP), and heart rate, as well as standing SBP, DBP and heart rate. The supine BP and heart rate should be measured first after the subject has been lying down for  $\geq 5$  minutes. The subject should then be asked to stand and the standing BP and heart rate should be measured after the subject has been standing for at least 2 minutes. Vital signs are to be recorded in the subject's study records.

Criterion for orthostatic hypotension is defined as a 20% increase of the mean arterial pressure.

The following measurements for vital signs are considered normal ranges for this study. It is expected that the values will generally be within the normal range as indicated below, however minor deviations, where they are not considered to be clinically significant as per the investigator, are acceptable.

|                    |                          |
|--------------------|--------------------------|
| SBP                | 90 – 139 mmHg            |
| DBP                | 45 – 89 mmHg             |
| Heart Rate         | 40 – 100 bpm             |
| Respiration Rate   | 16 – 20 breaths per min. |
| Temperature (oral) | 33.3 – 37.7°C            |

### 9.3.3.3 Electrocardiogram

All 12-lead ECGs will be complete, standardized recordings performed at specified timepoints indicated in Sections 9.1 and 9.2. The subject must rest in a supine position for  $\geq 5$  minutes before the ECG is obtained. ECG tracings (paper or electronic) will be reviewed and interpreted by a qualified clinician. ECG tracings and results (ventricular rate, PR, QRS, QT, QTcF intervals and investigator's interpretation) are to be included in the subject's study records.

#### **9.3.3.4 Columbia - Suicide Severity Rating Scale (C-SSRS)**

Administration and review of the C-SSRS will be performed by a qualified clinician at the specified timepoints indicated in Sections 9.1 and 9.2. C-SSRS (Baseline, version 1/14/09) will be administered at the Final Screening Visit and C-SSRS (Since Last Visit, version 1/14/09) will be administered thereafter. Results are to be included in the subject's study records. In the opinion of the investigator, any subjects who pose a serious safety risk to themselves will be managed according to the study site's Standard Operating Procedures (SOPs) for follow-up treatment and reporting.

#### **9.3.4 Clinical Laboratory Tests**

Table 9-2 summarizes the laboratory tests to be evaluated in the study. All laboratory reports must be reviewed by the investigator, and any abnormalities must be assessed for clinical significance. Results are to be included in the subject's study records.

**Table 9-2 Summary of Clinical Laboratory Test**

| Hematology                                                                  | Biochemistry                                       | Urinalysis                      | Serology                                                                                                                              |
|-----------------------------------------------------------------------------|----------------------------------------------------|---------------------------------|---------------------------------------------------------------------------------------------------------------------------------------|
| Red Blood Cell count (RBC)
White Blood Cell count (WBC) WBC differential | Total Protein                                      | Hydrogen ion concentration (pH) | Hepatitis B surface antigen                                                                                                           |
| Hemoglobin                                                                  | Albumin                                            | Specific gravity                | HIV                                                                                                                                   |
| Hematocrit                                                                  | Calcium                                            | Protein                         | Hepatitis C antibody                                                                                                                  |
| Mean Corpuscular Hemoglobin (MCH)                                           | Inorganic phosphorus                               | Glucose                         |                                                                                                                                       |
| Mean Corpuscular Hemoglobin Concentration (MCHC)                            | Cholesterol (total, LDL, HDL)                      | Ketones                         | Pregnancy                                                                                                                      |
| Red cell distribution width (RDW)                                           | Triglycerides                                      | Leukocyte esterase              | Serum/urine pregnancy (β-HCG)                                                                                                         |
| Mean Corpuscular Volume (MCV)                                               | Serum glutamic-pyruvic transaminase (SGPT/ALT)     | Nitrites                        |                                                                                                                                       |
| Platelet count                                                              | Serum glutamic-oxaloacetic transaminase (SGOT/AST) | Bacteria                        | Toxicology                                                                                                                     |
| Reticulocyte count                                                          | Electrolytes (Na, K, Mg, Cl) and Bicarbonate       | Occult blood                    | Saliva alcohol screen                                                                                                                 |
|                                                                             | Blood Urea Nitrogen (BUN)                          | WBC/high-power field            | Urine cotinine screen                                                                                                                 |
|                                                                             | Blood glucose                                      | Crystals                        | Urine drug screen (amphetamine, cocaine, barbiturates, methadone, benzodiazepines, MDMA, morphine/opiates, PCP, methamphetamine, THC) |
|                                                                             | Uric Acid                                          | Casts                           |                                                                                                                                       |
|                                                                             | Total and direct bilirubin                         | Epithelial cells                |                                                                                                                                       |
|                                                                             | Alkaline phosphatase (ALP)                         | Mucous Thread                   |                                                                                                                                       |
|                                                                             | Lactate dehydrogenase (LDH)                        |                                 |                                                                                                                                       |
|                                                                             | Gamma Glutamyl Transpeptidase (GGT)                |                                 |                                                                                                                                       |
|                                                                             | Creatinine Phosphokinase (CPK)                     |                                 |                                                                                                                                       |
|                                                                             | Serum Creatinine                                   |                                 |                                                                                                                                       |

#### 9.3.4.1 Serology Screen

A blood sample will be collected at the Initial Screening Visit for Hepatitis B surface antigen, HIV screening and serum antibodies to hepatitis C. In the event that the HIV results are positive, the study site must follow appropriate study site specific SOPs for informing the subject of their status, follow-up treatment and reporting.

#### 9.3.4.2 Urine Cotinine Screen

A urine sample will be collected at the Initial Screening Visit to screen for tobacco use.

#### 9.3.4.3 Saliva Alcohol Screen

Saliva alcohol screens will be performed at specified timepoints indicated in Sections 9.1 and 9.2 to test for alcohol levels.

#### 9.3.4.4 Urine Drug Screen

A urine sample will be collected at specified timepoints indicated in Sections 9.1 and 9.2 to

screen for controlled substances. The following controlled substances will be tested: amphetamine, barbiturates, benzodiazepines, cocaine, methadone, morphine/opiates, methamphetamine, marijuana (THC), phencyclidine (PCP), ecstasy (MDMA).

#### **9.3.4.5 Serum/Urine Pregnancy**

For all female participants, serum/urine pregnancy samples will be drawn at specified timepoints indicated in Sections 9.1 and 9.2.

#### **9.3.4.6 Hematology and Biochemistry**

Blood samples will be drawn preferably under fasting conditions for routine hematology and biochemistry (see Table 9-2) at specified timepoints indicated in Sections 9.1 and 9.2.

#### **9.3.4.7 Urinalysis**

Urine samples will be collected for routine urinalysis at specified timepoints indicated in Sections 9.1 and 9.2.

### **9.3.5 Pharmacodynamics (PD) Assessments**

#### **9.3.5.1 MRI Assessments with Ketamine Infusion**

BOLD fMRI assessments with ketamine infusion will be conducted at specified timepoints indicated in Sections 9.1 and 9.2. The fMRI scanning time at the second session should be within  $\pm 2$  hour of the scanning time at the first session.

Subjects will be under close observation by an investigator, with visual and verbal contact maintained throughout the MRI session. Subjects who experience distress or become claustrophobic in the magnet will be removed immediately from the magnet room. At least one physician will be present during the course of the procedure. All staff involved in conduct of MRI scan will be thoroughly familiar with the study site's emergency plan.

Total duration of MRI scanning will be approximately 40 minutes. The scanning will be comprised of a 10-minute structural MRI scan (a 7-minute structural scan, a 2-minute phase map, and 2 sets of 30-second BOLD top-up scans), a 15-minute pre-ketamine BOLD fMRI scan, and a 15-minute post-ketamine BOLD fMRI scan. During the 15-minute pre-ketamine BOLD fMRI scan, subjects will receive continuous intravenous administration (i.e., drip) of saline to keep their intravenous line open for subsequent ketamine infusion. Subjects will be under constant monitoring by ECG and pulse oximeter, as well as by frequent BP measurements throughout the MRI scan, which will be recorded in the subject's study records. The make and model of the MRI scanner used, date and time of initiation and cessation of MRI scanning are to be recorded in the subject's study record.

### 9.3.5.1.1 Ketamine Infusion

Subjects will be administered with a racemic ketamine hydrochloride intravenous constant infusion. Ketamine will be infused as 0.23 mg/kg bolus over 1 minute in accordance with the subject's weight (measured at each ketamine session day) inside the MRI scanner. Ketamine dosage should not exceed 20 mg per subject per session.

Ketamine infusion and subsequent 15-minute fMRI scan will be performed in the presence of the investigator. The date and time of initiation of ketamine infusion are to be recorded in the subject's study record.

### 9.3.5.1.2 Image Acquisition

A MRI manual is being provided in a separate document to take precedence over the protocol language in this section. Any revisions to the MRI manual that are implemented during the study will be described in the final report.

Subjects will be scanned using a 3.0T MRI scanner. An approximate 40-minute, eyes-open, resting-state BOLD fMRI scan will be acquired using echo-planar imaging (EPI). A total of 900 image volumes of 23 near-axial slices (4-mm thickness, aligned to the anterior commissure-posterior commissure) will be acquired per session; echo time (TE) = 30 msec; repetition time (TR) = 2000 msec; flip angle = 75°, in-plane resolution = 3.3 mm; matrix size = 64 x 64; field of view (FOV) = 21.1 x 21.1 cm. A T1 weighted SPGR scan will also be acquired (TE = 2.3msec, TR = 2400 msec, flip angle = 12°, 0.8 mm isotropic voxels, matrix size = 300 x 300, FOV = 24 x 24 cm).

### 9.3.5.1.3 Image Processing and Modeling

A MRI manual is being provided in a separate document to take precedence over the protocol language in this section. Any revisions to the MRI manual that are implemented during the study will be described in the final report.

No treatment identifiable information is encoded in the imaging data files and all MRI image analyses will be blinded to treatment condition. The data manager will maintain the randomization table for each imaging treatment assignment set until study database is locked.

fMRI data will be preprocessed using FSL (<https://fsl.fmrib.ox.ac.uk/fsl/fslwiki>) and Matlab (<https://www.mathworks.com/>). Preprocessing of fMRI data includes slice time correction, motion correction, spatial smoothing (5 mm full width at half maximum Gaussian kernel), and high-pass filtering with a cutoff of 1200 s will be applied to the data to minimize the influence of very-low-frequency noise and scanner drift. Linear regression is performed using 27 motion parameters including 3 translations, 3 rotations, lag +1 derivatives, lag -1 derivatives, quadratic term, the mean relative motion, and the mean absolute motion. The model residual is then used

for evaluating all ketamine-evoked responses. Linear registration to the subject's high resolution SPGR image (6 degrees of freedom) and to the MNI152 standard space template (12 degrees of freedom) is performed to generate spatial transforms.

A ROI analysis is performed using the mid-cingulate cortex, which had the largest BOLD response at 50 ng/mL ketamine in the study conducted by De Simoni. Two seeds are placed at (MNI: 4,2,42) and (MNI: -4,2,42) and spherically dilated by 8 mm. The masks are transformed to the individual subject's functional space and multiplied by the gray matter partial volume map to minimize the contribution of non-gray voxels. For each subject, the BOLD time series is extracted from the ROI and fit to a three parameter gamma model:

$$y(t) = a \left( \frac{t}{t_{\max}} \right)^{b \cdot t_{\max}} e^{(t_{\max} - t) \cdot b}$$

where  $t_{\max}$  is time of maximum response,  $a$  is amplitude of the response, and  $b$  is the shape parameter of the function. The fitted response is converted to a percent signal change by normalizing to the mean. Peak BOLD response is defined as the maximum value of the fitted gamma model. Mean BOLD response is defined as the area under the curve of the gamma model divided by the scan duration (600 sec). The mean BOLD response is highly correlated to the peak BOLD response but is less sensitive to outliers when comparing groups. A whole brain analysis is performed using multiple linear regression by constructing a gamma regressor with parameters equal to the group mean ( $b = 0.009$ ,  $t_{\max} = 226$  sec). The beta images from the contrast of the first regressor will be used in the group-level analyses.

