### 8.1.4 Blinding

This study is a single-blind study and all subjects are blinded to the treatment assignment information. The investigator (except for blinded investigators described below) and the sponsor will have knowledge of the treatment assignment.

Blinded investigators:

- Investigators and/or trained designees who are responsible for administering and scoring of behavioral assessments described in Section 9.3.5.2 will be blinded from treatment assignment information until the study database is locked.
- Investigators and/or trained designees who are responsible for BOLD fMRI data scoring will be blinded from treatment assignment information until the database is locked.

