## 10 STATISTICAL METHODS

In addition to this section of the study protocol, a more detailed statistical analysis plan (SAP) will also be provided in a separate document. If circumstances arise during the study that make these analyses inappropriate or if improved methods become available, the SAP will take precedence and may be revised, as needed. Any revisions (both alternative and additional methods) to the SAP that are used in the final report, and reasons for such revisions, will be described in the final report.

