### **10.5.3 Interim Data Transfer**

Interim data transfer for change in BOLD signals in pre-specified ROIs in resting fMRI will be conducted for every 12 first and second ketamine session sets of assessments (i.e. following completion of 12th, 24th, 36th, 48h, and 60th subjects). Each interim analysis result will be provided to the sponsor within 7 days following the completion of BOLD assessments of respective cut-off subjects.

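### The protocol lets the computation of the primary BOLD response be revised during the study and requires no freeze before ROI results reach a sponsor that knows allocation

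*Protocol*

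**What the plan says.** Protocol section 9.3.5.1.3 (Image Processing and Modeling) sets the filter, smoothing, motion regression, ROI seeds, gamma response model and two response summaries, peak and mean. It opens with "A MRI manual is being provided in a separate document to take precedence over the protocol language in this section", followed by "Any revisions to the MRI manual that are implemented during the study will be described in the final report". That report is the only condition attached to a revision.

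Section 10 provides for a separate SAP. If the planned analyses become inappropriate or better methods appear, "the SAP will take precedence and may be revised, as needed". Revisions used in the final report, and the reasons for them, are to be described there.

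Section 10.5.3 transfers change in ROI BOLD after the 12th, 24th, 36th, 48th and 60th subjects: "Each interim analysis result will be provided to the sponsor within 7 days following the completion of BOLD assessments of respective cut-off subjects". Under section 8.1.4 the investigator (apart from the blinded raters and scorers) "and the sponsor will have knowledge of the treatment assignment".

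There are safeguards. In section 8.1.4 the staff "responsible for BOLD fMRI data scoring will be blinded from treatment assignment information until the database is locked", and section 9.3.5.1.3 states that "all MRI image analyses will be blinded to treatment condition", with the data manager keeping the randomisation table until lock.

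Sections 6.2.1 and 10.5.1 name the ROIs (ACC and anterior insula). Section 10.5.1 sets the model: ANCOVA of change from baseline at Day 6 on baseline and treatment.

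**The concern.** Leaving image-processing detail to a manual, or analysis detail to a SAP, is normal practice and is not the complaint. The complaint is a combination that the protocol itself sets up. A document that overrides the definition of the primary variable stays revisable while results on that variable go, in five instalments, to a party that knows who received what. No date is set after which the definition is closed, and revisions are not reserved to people without access to results.

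Section 10.5.1 treats a statistically significant negative change against placebo as support for the hypothesis. Such a test has its nominal error rate only if the variable was fixed independently of the results. If the variant is settled after early results are known, the subjects who prompted the choice are also counted in the final test, so the p-value and confidence interval are somewhat too favourable. Describing the revision in the final report makes it visible but does not restore the error rate.

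**Working it through.** **1. What each document can change.**

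| Element | Where stated | Open to the manual? | Open to the SAP? |
|---|---|---|---|
| ROI names | 6.2.1, 10.5.1 | No | Wording in 10.5.1 only |
| Change from baseline, covariate, ANCOVA, contrasts | 10.5.1 | No | Yes, under the stated conditions |
| ROI mask, preprocessing, gamma model, peak and mean, time window | 9.3.5.1.3 | Yes | Not through section 10, except that 10.5.1 does not say which summary is analysed |

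The manual's precedence covers only the section in which it is stated. What it leaves open is how BOLD is computed.

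**2. Whether real choices remain.** Three do.

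- *Region.* 9.3.5.1.3 describes a mid-cingulate ROI with two seeds, whereas 6.2.1 and 10.5.1 name ACC and anterior insula.
- *Summary.* 9.3.5.1.3 defines both peak and mean; the outcome in 10.5.1 is just BOLD.
- *Window.* The mean divides the area under the curve by 600 sec, but the post-ketamine scan in 9.3.5.1 lasts 15 minutes, or 900 sec.

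The window can be sized with the protocol's group values b = 0.009 and t_max = 226 sec. The curve relative to peak is (t/226)^(0.009 × 226) × exp((226 − t) × 0.009). Numerical integration gives an area of 373.2 over 0-600 sec and 408.2 over 0-900 sec. Mean as a share of peak is then:

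- 373.2/600 = 0.62
- 408.2/600 = 0.68
- 408.2/900 = 0.45

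Changing only the divisor rescales every subject alike and leaves the p-value unchanged. Changing the integration window, the mask or the summary can change the test, because the fitted curves differ between subjects.

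**3. Who sees what, and when.** The sponsor gets ROI BOLD results at subjects 12, 24, 36, 48 and 60 and knows allocation. If allocation tracks 5:5:2, the first 12 subjects comprise 12 × 5/12 = 5, 5 and 12 × 2/12 = 2 on placebo. Section 10.5.3 does not say that the results are split by arm. That the sponsor can split them is an inference from 8.1.4.

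**4. Size.** The protocol states no alpha, SD, effect size or correlation, so there is no figure of its own to reproduce. The following is illustrative.

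Assumptions: null data; 60 subjects in blocks of 5:5:2; K candidate definitions with pairwise correlation r; baseline-to-Day-6 correlation 0.6; one ROI; one dose-placebo contrast. The test statistic is

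t = [(ȳ_dose − ȳ_plac) − β(x̄_dose − x̄_plac)] / √{s²[1/n_dose + 1/n_plac + (x̄_dose − x̄_plac)²/S_xx]}

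where y is change, x is baseline and S_xx is the within-group sum of squares of x. At n = 60 the degrees of freedom are 60 − 4 = 56. The definition with the most negative t at the interim is carried forward, and a false positive is t < −t(0.975, 56) at n = 60. The nominal rate is 2.5%. There were 20,000 trials per row.

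| K | r | No choice | Chosen at 12 | Chosen at 24 | Chosen on final data |
|---|---|---|---|---|---|
| 3 | 0.9 | 2.6% | 3.1% | 3.4% | 4.3% |
| 3 | 0.7 | 2.4% | 3.5% | 4.2% | 5.3% |
| 6 | 0.9 | 2.6% | 3.6% | 4.3% | 5.6% |
| 6 | 0.7 | 2.5% | 4.3% | 5.8% | 8.2% |

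The simulation standard error is at most about √(0.08 × 0.92/20,000) = 0.2 percentage points. Choice at 12 to 24 subjects therefore gives roughly 3-6%.

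**The case against.** The best case for the plan has four parts.

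- *The manual and SAP are not on view.* The protocol describes the manual as being supplied alongside it, and version control usually sits in such documents. Exclusion criterion 13 also needs an ACC peak response at the Final Screening Visit, so a working pipeline must exist before anyone is randomised. A reader might infer that the primary outcome was in fact never fixed. The documents do not support that; they show only that this protocol does not require it to be fixed. A working pipeline is, however, not a frozen one.
- *The SAP clause is narrower than the manual clause.* It is conditional and requires reasons. A reader might infer that both documents may be changed freely, which is wrong for the SAP. Even so, the condition that better methods have appeared sets no cut-off date.
- *Scoring and image analysis are blinded until lock.* This protects the processing of each scan. It does not stop someone who knows allocation from prompting a change of definition, and no section says who may revise the manual.
- *The study is exploratory.* Section 10.3 calls most analyses descriptive, and section 15.1 describes an exploratory phase I study. That lowers the stakes, but 10.5.1 still specifies tests and confidence intervals.

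The largest simulated figures, about 8%, describe free choice on the final data among six variants. They should not be quoted for a choice made at an early transfer. The protocol's remark that mean and peak are closely correlated points to the lower end of the range, at least for that pair.

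**Conclusion.** The point stands in limited form. The protocol lets the computation of the primary BOLD response (mask, preprocessing, peak or mean, time window) be revised during the study. It requires no freeze before ROI results reach a sponsor that knows allocation, and blinded image analysis does not close that route. The ROI names and the ANCOVA are outside the manual's reach.

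A definition settled on results at 12 to 24 subjects would raise the one-direction error from 2.5% to roughly 3-6%. This rests on assumed values: 3 to 6 variants, correlations of 0.7 to 0.9 and a two-sided 5% level. It also supposes that the choice follows the results. The documents do not show that this happened or was intended, and nothing here should be read as saying so. The change is worth making because it removes the possibility at little cost.

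**What to change.** In Protocol section 9.3.5.1.3, replace the precedence sentence with a statement that, for the primary endpoint, the following are frozen before the first randomised subject, or at the latest before the first BOLD transfer, with the manual version archived:

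- the ACC and anterior insula masks;
- preprocessing, response model and time window;
- one named response summary, peak or mean.

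In the same edit, reconcile the mid-cingulate ROI with 6.2.1 and 10.5.1, and the 600 sec duration with the 15-minute post-ketamine scan.

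In section 10, require the SAP's primary-endpoint section to be signed by the same date.

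Later changes to either are sensitivity analyses. The exception is correction of a processing error, made by staff blinded to allocation, applied to all scans and reported beside the original result.

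The cost is wording and earlier sign-off, with no change to sample size or study procedures. The downside is that a better pipeline found later can only be supportive.
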